
### Research Questions, Hypotheses, and Objectives

This project is intended to scale-up implementation and delivery of AFFIRM, an 8-session manualized group coping skills intervention focused on reducing sexual risk behaviors and psychosocial distress among SGMY. This project aims to decrease sexual risk taking, depression, and internalized homophobia and increase levels of sexual self-efficacy and proactive coping among SGMY (ages 14-29 years). This project has the following research questions:

To what extent can AFFIRM be feasibly implemented in a range of practice settings, such as community health centers, family health teams, and community-based organizations?What are the facilitative conditions and implementation barriers to effective delivery of AFFIRM?How does participation in an affirmative coping skills intervention (AFFIRM) impact the psychosocial distress and sexual self-efficacy of SGMY?

Given these research questions, the study has the following hypotheses:

Hypothesis 1: AFFIRM can be feasibly implemented in a range of practice settings, and SGMY will have high rates of acceptability of the intervention.

Hypothesis 2: SGMY participating in AFFIRM will show significantly greater decreases in psychosocial distress (eg, internalized stigma and depression) compared with wait-listed controls (ie, SGMY attending existing community programs).

Hypothesis 3: SGMY participating in AFFIRM will show significantly higher levels of sexual self-efficacy and coping compared with wait-listed controls.

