### Eligibility Criteria

#### Inclusion and Exclusion Criteria

Inclusion criteria are as follows:

Aged 14 to 29 years at the time of screeningIdentifies as a sexual and/or gender minorityReads, writes, and speaks fluent EnglishIs interested in participating in the 8-session AFFIRM Intervention.

Exclusion criteria are as follows:

Assessed by the Facilitation Team to be in crisis (ie, high risk of suicidality)Warranting a more intensive intervention

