#### Discontinuation Criteria

Participants who are in crisis (eg, actively suicidal) at any point during their in-person participation in the AFFIRM intervention are immediately assessed, and appropriate steps are taken to address their individual situation—up to and including being taken to local support services or hospitals by AFFIRM facilitators. Participants who are in crisis are withdrawn from the intervention and the study. A distress protocol (Multimedia Appendix 1) and crisis response form (Multimedia Appendix 2) have been developed for AFFIRM facilitators and is systematically implemented throughout the intervention when participants indicate signs of distress. Importantly, to enhance participants’ safety and well-being, as part of the Web-based data collection, participants are asked at various points if they need immediate help and are provided with immediate resources, including national crises organizations (such as Kids Help Phone Canada or the Trevor Project) with 24-hour counseling via phone, chat, and/or SMS text messaging (short message service, SMS).

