### Outcomes

#### Primary

The primary outcomes of this study are feasibility and acceptability. Feasibility will be measured by (1) number of sites that implement AFFIRM; (2) number of times each site runs the AFFIRM intervention; (3) availability of facilitators; and (4) number of participants that enroll, commence, and complete the intervention. Acceptability will be assessed through mixed-method participant and facilitator evaluations.

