#### Exploratory

Exploratory outcomes include changes in sexual health self-efficacy and capacity, mental health indicators, internalized homophobia, stress appraisal, proactive and active coping, and hope. These outcomes will be assessed through measures such as: the Sexual Health Capacity Scale [100], the Abstinence and Protection Self-Efficacy Scale [101], the Beck Depression Inventory-II [102], the Diagnostic and Statistical Manual of Mental Disorders-V (DSM-V) Self-Rated Level 1 Cross-Cutting Symptom Measure–Child [103], the Stress Appraisal Measure for Adolescents [104], the Brief COPE [105], the Proactive Coping Inventory for Adolescents-A [106], the Adult Hope Scale [107], the Internalized Homophobia Scale [108], the Current Mood Scale [109], the Everyday Discrimination Scale [110], and the LGBTQ Microaggession Scale [111] (see Table 1).

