### Participant Timeline

Table 2 shows the schedule of events. Participants complete a Web-based screening questionnaire, which includes their preferred site to participate in AFFIRM. For every 2 participants allocated to the intervention-only group, 1 participant is allocated to the wait-list group. The intervention-only group completes 4 data collection time points (pretest, posttest, 6-month follow-up, and 12-month follow-up). The wait-list group completes 5 data collection time points (prewait, pretest, posttest, 6-month follow-up, and 12-month follow-up). The prewait survey is completed immediately following their wait-listed control allocation, so that the pretest for the wait-list group serves as the follow-up on outcomes for the control group. Participants complete the pretests and posttests before the first week and at the last week of the intervention, respectively. The Web-based pretest is completed independently shortly before the first group session. The posttest is completed on tablets (eg, Android tablets) at the intervention location following the final group session. Participants complete the prewait (if applicable), the 6-month follow-up, and the 12-month Web-based independent follow-up. Participants are reminded to participate via email and provided the link to the survey. If participants do not participate following the initial email, up to 2 follow-up emails are sent as reminders for each time point. The follow-up emails are sent at 2 weeks and 4 weeks after the initial email (ie, every 2 weeks for 1 month). If participants indicated in their Web-based screening that SMS text message or phone call is their preferred form of communication, they also receive follow-up SMS text messages at 2 to 4 weeks after the initial email.

**Table 2 table2:** Schedule of events.

Visit details		Screening period			Study period (facilitator meeting; 8 weekly, 1-hour sessions)			Follow-up period	
Visit name		Screening survey	Prewait	Pretest	Orientation	Sessions 1-8	Posttest	6-month follow-up	12-month follow-up
Visit number.		−3	−2	−1	0	1,2,3,4,6,7,8	8	9	10
Week number		-8 to 0	-8 to 0	-8 to 0	0	1-8	8	32	56
Day number		−56 to 0	−56 to 0	−56 to 0	1-56	1-56	1-56	+224 to +238	+392 to +406
Visit window		±56	±14	±0	±0	±0	±0	±14	±14

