### Harms

As a psychosocial study, risks for adverse effects are negligible or nonexistent. The study’s distress plan, discussed above, will be used if participants present in crisis.

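### A crisis during AFFIRM ends study participation as well as the group, so this rule removes depression scores from the AFFIRM period only; the bias is probably small and cheap to reduce

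*Protocol article*

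**What the plan says.** All references are to the protocol article.

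- **Discontinuation Criteria.** Anyone in crisis while attending AFFIRM in person is assessed at once and helped, if necessary by being taken to local services or hospital. Then: "Participants who are in crisis are withdrawn from the intervention and the study". The same section says of the web surveys that "participants are asked at various points if they need immediate help and are provided with immediate resources"; no withdrawal is attached to that prompt.
- **Participant Timeline.** The AFFIRM contrast is pretest to posttest, with further surveys at 6 and 12 months. Wait-listed youth complete an extra prewait survey, "so that the pretest for the wait-list group serves as the follow-up on outcomes for the control group".
- **Research Questions, Hypotheses, and Objectives.** Hypothesis 2 is that "SGMY participating in AFFIRM will show significantly greater decreases in psychosocial distress (eg, internalized stigma and depression) compared with wait-listed controls".
- **Exploratory outcomes.** "Exploratory outcomes include changes in sexual health self-efficacy and capacity, mental health indicators"; the BDI-II is among the measures listed.
- **Results.** Analyses are paired t tests and repeated measures mixed models. Imputation is described for data judged missing at random.

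**The concern.** Stopping the group for a youth in crisis is a clinical decision and is not questioned here. Stopping outcome collection is a separate decision, and the article gives no reason for it.

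The consequence is one-sided. The withdrawal sentence belongs to a rule about crises arising during AFFIRM sessions. The control window ends before the first session. Wait-listed youth come under the rule only after they cross over, by which time their control measurements have been taken.

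The reason for the loss, such as active suicidality, is also closely tied to the outcome being compared. If the unseen posttests are worse than the others, leaving them out makes the AFFIRM change in depression look better than it was. A mixed model or imputation that assumes missingness at random can use the pretest, but it cannot recover a deterioration that happened afterwards.

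**Working it through.** **Comparing the two windows**

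| | AFFIRM period | Wait period |
|---|---|---|
| Start | pretest | prewait survey |
| End | posttest after the last session, then 6 and 12 months | pretest, before any session |
| Stated response to a crisis | withdrawn from group and study | resources offered in the web survey; no withdrawal stated |

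**Size**

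The article gives no crisis rate, BDI-II spread or pre-post correlation, so there is no figure of its own to reproduce.

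Inputs from the article: about 300 participants (Sample Size) and a ratio of about 2:1 (Allocation), which gives about 200 intervention-only and 100 wait-list.

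Assumed inputs:
- share withdrawn in crisis, p = 1%, 3% or 5%, which is 2, 6 or 10 of 200
- posttest of crisis youth minus that of the others, dpost = 10 to 20 BDI-II points
- pretest of crisis youth minus that of the others, dpre = 0 or 10 points
- pre-post correlation r = 0.6, with equal spread before and after
- SD of change 9 to 12 points

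*Mixed model keeping the pretest:* shift = p × (dpost − r × dpre).
- dpre = 0: from 0.01 × 10 = 0.1 to 0.05 × 20 = 1.0. At 3%: 0.3 to 0.6.
- dpre = 10: from 0.01 × (10 − 6) = 0.04 to 0.05 × (20 − 6) = 0.7. At 3%: 0.12 to 0.42.

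A simulation (200 youth, 4000 runs, maximum likelihood on pre and post) gave 0.10 to 1.00 and 0.04 to 0.70, in agreement.

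*Paired t test on complete pairs:* shift = p × (dpost − dpre), which is 0.1 to 1.0 at dpre = 0 and 0 to 0.5 at dpre = 10.

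*Against sampling error:* SE = SD × √(1/200 + 1/100) = SD × 0.1225, which is 1.10 at SD 9 and 1.47 at SD 12, ignoring clustering.
- Largest shift: 1.0/1.10 = 0.91 SE, or 1.0/1.47 = 0.68 SE.
- Largest shift with dpre = 10: 0.7/1.10 = 0.64 SE.
- At 3% with dpre = 10: 0.12/1.47 = 0.08 to 0.42/1.10 = 0.38 SE.

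*Cross-check in SD units, completers only:* suppose a share c is lost and their change would have been D SD worse. The bias is c × D, and SE = √(1/100 + 1/(200(1 − c))). With no true effect, a nominal two-sided 0.05 test rejects with probability Φ(b/SE − 1.96) + Φ(−b/SE − 1.96), where b = c × D.
- c = 2%, D = 1 to 2: bias 0.02 to 0.04 SD, error 0.053 to 0.062.
- c = 5%, D = 1 to 2: bias 0.05 to 0.10 SD, error 0.069 to 0.128.

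This ignores the pretest information that the planned mixed model would use, so it is the less favourable calculation.

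**The case against.** **Control losses may not be zero.** The Harms section applies the distress plan to participants who present in crisis, without limiting it to sessions. A wait-listed youth in crisis might be held back or not answer the pretest. The net bias is the difference between the two losses. This stands: the figures above set crisis-related control loss to zero and are upper bounds in that respect. A reader might infer that no wait-listed youth is lost through crisis. The article supports only the narrower statement that its withdrawal rule removes none of their control-window scores.

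**The largest figure needs an unlikely combination.** It requires 5% withdrawn although youth in crisis are excluded at entry, a 20-point gap, and pretests no different from everyone else's. Positive clustering within groups of 6 to 10 would enlarge the SE and lower the ratios further. This also stands.

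**Little rests on this outcome.** Depression change is exploratory, the sample was set mainly for implementation outcomes, and allocation is not randomised. Correct, and it limits the weight of the point.

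**Stopping research contact may be protective.** The surveys take about 20 minutes and cover depression and discrimination, and some participants are as young as 14. This is a fair reason for conditions on later contact. It is a weaker reason for ending contact permanently, because a survey months later can be offered once it is safe and can be declined.

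**Two further inferences go too far.** Feasibility item (4), the "number of participants that enroll, commence, and complete the intervention", does not separate crisis withdrawals from other non-completion, so a reader might infer that such events would be hidden. A breakdown by reason is detail that a condensed article may omit, and a crisis response form is already in use. A reader might also take "As a psychosocial study, risks for adverse effects are negligible or nonexistent" in the Harms section as contradicting the crisis rule. It does not: the wording is unsupported, but crises can occur as background events without the study causing them. How data not missing at random are handled can likewise be left to the analysis plan.

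**Conclusion.** The point holds in a limited form. The article explicitly ends study participation for youth in crisis during AFFIRM, and nothing equivalent is stated for the wait period. The scores lost are plausibly related to depression, and the likely direction favours AFFIRM on Hypothesis 2.

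Under assumed crisis withdrawal of 1% to 5%, the shift is about 0.04 to 1.0 BDI-II points. That is at most about 0.9 SE and in most of the scenarios well below. The direction depends on the unseen scores being worse, and the size on inputs that the article does not give. A reader might infer that the rule could by itself produce a false finding of benefit; the article supplies no crisis rate that would support this. It is a cheap improvement to an exploratory comparison and does not threaten the primary outcomes of feasibility and acceptability.

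**What to change.** Amend the sentence in Discontinuation Criteria so that a crisis ends the intervention only. State that the posttest, 6-month and 12-month surveys are still offered once this is clinically safe and if the participant agrees. The posttest is normally done on a tablet at the site, so for these youth it would be sent as a web link, as the follow-ups already are. The surveys already ask about immediate help and give crisis resources.

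**Cost:** one sentence and no new instruments. It may need an ethics amendment while data collection is under way. Some youth will decline, so the loss is reduced but not removed. Scores not collected now cannot be recovered later.

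**Optional, and not part of the point:** count crisis withdrawals on a separate line of the completion figures, and replace the opening statement of Harms with one saying that such events will be counted and reported.

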#### Protocol Adherence Strategy

The Core Facilitation Team (delivering the AFFIRM intervention) comprises social workers with a master’s degree who are trained in AFFIRM, who meet weekly with the principal investigator to review study progress and ensure protocol adherence. All iterations of AFFIRM implemented in this study are cofacilitated by (1) one of the members of the Core Facilitation Team and (2) 1 representative of the CCAS (eg, a social worker, nurse, or community worker) where the intervention group is being held or another community-based professional, all of whom are trained in the AFFIRM intervention.

#### Concomitant Care and Interventions

There are no restrictions on participant involvement in other studies and/or interventions as a result of their participation in this project. While this prevents accounting for confounding factors (eg, combined effect of participating in another intervention), the geographic context of services in Ontario is such that it is unlikely that participants would have access to SGMY-specific affirmative interventions outside of this study.

### Outcomes

#### Primary

The primary outcomes of this study are feasibility and acceptability. Feasibility will be measured by (1) number of sites that implement AFFIRM; (2) number of times each site runs the AFFIRM intervention; (3) availability of facilitators; and (4) number of participants that enroll, commence, and complete the intervention. Acceptability will be assessed through mixed-method participant and facilitator evaluations.

#### Secondary

This study’s secondary outcome is implementation fidelity, that is, how closely AFFIRM facilitators adhere to the manualized intervention. This will be assessed through analysis of session audio recordings and facilitator process notes by analysts separate from the Core Facilitation Team.

#### Exploratory

Exploratory outcomes include changes in sexual health self-efficacy and capacity, mental health indicators, internalized homophobia, stress appraisal, proactive and active coping, and hope. These outcomes will be assessed through measures such as: the Sexual Health Capacity Scale [100], the Abstinence and Protection Self-Efficacy Scale [101], the Beck Depression Inventory-II [102], the Diagnostic and Statistical Manual of Mental Disorders-V (DSM-V) Self-Rated Level 1 Cross-Cutting Symptom Measure–Child [103], the Stress Appraisal Measure for Adolescents [104], the Brief COPE [105], the Proactive Coping Inventory for Adolescents-A [106], the Adult Hope Scale [107], the Internalized Homophobia Scale [108], the Current Mood Scale [109], the Everyday Discrimination Scale [110], and the LGBTQ Microaggession Scale [111] (see Table 1).

### Data Collection

AFFIRM participant data are exclusively collected using Web-based surveys, *each of which takes approximately 20 min to complete*. However, data collection takes place in 2 different settings: (1) via tablets (eg, Android tablets) while at the intervention locations (ie, some Web-based screenings, some pre- and posttests); and (2) independently Web-based (eg, some Web-based screenings, some pretests, or follow-ups). Secure collection of data is facilitated by the use of software with secure servers (Qualtrics). Instead of a unique identifier, which participants could forget over the course of the year, participants report their name, age, date of birth, 2 email addresses, gender identity, and sexual orientation at each time point.

### Measures

All measures are completed at all time points, including demographics, as identities and circumstances are generally very flexible for SGMY because of their developmental stage, marginalized sexual and/or gender identities, and contextual circumstances. Measures include the following: (1) *demographics* (eg, age, sexual identity, gender identity, ethno-racial identity, and socioeconomic-status); (2) *sexual health self-efficacy and capacity*, including sexual health capacity [100] and abstinence and protection self-efficacies [101]; (3) *mental health*, including current mood [109], depression [102], and DSM-V cross-cutting symptoms [103]; (4) *coping*, including proactive coping [105] and coping strategies such as active coping, denial, and humor [106]; (5) *stress appraisal*, including perceiving stress as challenge or threat, and seeking out resources to overcome stress [104]; (6) *hope*, including agency and planning to meet goals [107]; (7) experiences with everyday discrimination [110]; (8) *internalized homophobia* [108]; (9) microaggressions, including interpersonal and environmental microaggressions [111]; (10) *AFFIRM Satisfaction Survey,* a 20-item questionnaire developed for AFFIRM completed after intervention delivery, which includes questions regarding (1) satisfaction, (2) overall experience, and (3) suggestions for improvement. For details of adaptation of existing survey measures, please see Table 1.

**Table 1 table1:** Survey instruments.

Construct	Scale, study	Items	Modification
Sexual health self-efficacy and capacity	Sexual Health Capacity Scale [100]	5	Change scale from 5-point (1-5) to 4-point (1-4); Excluded 2 items; Added 1 item: “I understand how my mental and sexual health are connected.”
	Abstinence Self-efficacy Scale [101]	4	Excluded 6 items; Wordings modified
	Protection Self-efficacy Scale [89]	8	Added 4 items: “I can ask for/get a test for HIV and STIs from a doctor, Planned Parenthood, or a clinic.”; “I can read or think about my sexual health plan before having sex.”; “I can access/get information about my sexual health (websites, agencies, trusted adults, professionals, or friends).”; “I can manage my own sexual health.”; Wordings modified
Mental health	Beck Depression Inventory-II [102]	20	No modifications
	DSM-5^a^ Self-Rated Level 1 Cross-Cutting Symptom Measure—Child [103]	20	Excluded 5 items from section 9 (Psychosis) and 10 (Repetitive Thoughts and Behaviors); Slightly modified 1 item
	Current Mode Scale [109]	6	Wordings simplified
Coping	Brief COPE [105]	28	2 items slightly modified
	Proactive Coping Inventory for Adolescents-A—Reflective Coping subscale [106]	11	4 items slightly modified
Stress appraisal	Stress Appraisal Measure for Adolescents [104]	13	1 item excluded; 1 item slightly modified
Hope	Adult Hope Scale [107]	12	No modifications
Internalized homophobia	Internalized homophobia [108]	10	Separated into 2 sections for microaggressions toward sexual orientation and gender identity minorities
Discrimination and microaggressions	Everyday Discrimination Scale [110]	7	2 items excluded; 1 item slightly modified
	LGBTQ^b^ Microaggressions Scale—Interpersonal subscale [111]	10	Excluded 10 items; Separated into 2 sections for microaggressions toward sexual orientation and gender identity minorities
	LGBTQ Microaggressions Scale—Environmental subscale [111]	5	Excluded 2 items; Added 2 items: “In my online environment it was OK to make jokes about LGBTQ+ people.” and “I heard or read someone making fun of chosen pronouns.”

^a^DSM-5: Diagnostic and Statistical Manual of Mental Disorders, 5^th^ edition.

^b^LGBTQ: lesbian, gay, bisexual, transgender, and queer.

### Participant Timeline

Table 2 shows the schedule of events. Participants complete a Web-based screening questionnaire, which includes their preferred site to participate in AFFIRM. For every 2 participants allocated to the intervention-only group, 1 participant is allocated to the wait-list group. The intervention-only group completes 4 data collection time points (pretest, posttest, 6-month follow-up, and 12-month follow-up). The wait-list group completes 5 data collection time points (prewait, pretest, posttest, 6-month follow-up, and 12-month follow-up). The prewait survey is completed immediately following their wait-listed control allocation, so that the pretest for the wait-list group serves as the follow-up on outcomes for the control group. Participants complete the pretests and posttests before the first week and at the last week of the intervention, respectively. The Web-based pretest is completed independently shortly before the first group session. The posttest is completed on tablets (eg, Android tablets) at the intervention location following the final group session. Participants complete the prewait (if applicable), the 6-month follow-up, and the 12-month Web-based independent follow-up. Participants are reminded to participate via email and provided the link to the survey. If participants do not participate following the initial email, up to 2 follow-up emails are sent as reminders for each time point. The follow-up emails are sent at 2 weeks and 4 weeks after the initial email (ie, every 2 weeks for 1 month). If participants indicated in their Web-based screening that SMS text message or phone call is their preferred form of communication, they also receive follow-up SMS text messages at 2 to 4 weeks after the initial email.

**Table 2 table2:** Schedule of events.

Visit details		Screening period			Study period (facilitator meeting; 8 weekly, 1-hour sessions)			Follow-up period	
Visit name		Screening survey	Prewait	Pretest	Orientation	Sessions 1-8	Posttest	6-month follow-up	12-month follow-up
Visit number.		−3	−2	−1	0	1,2,3,4,6,7,8	8	9	10
Week number		-8 to 0	-8 to 0	-8 to 0	0	1-8	8	32	56
Day number		−56 to 0	−56 to 0	−56 to 0	1-56	1-56	1-56	+224 to +238	+392 to +406
Visit window		±56	±14	±0	±0	±0	±0	±14	±14

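### The posttest is fixed on site after the last session, so youth absent from it are likely under-represented, and the AFFIRM and wait-list follow-ups differ in place and moment

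*Protocol article*

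**What the plan says.** All places are in the protocol article.

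- **Posttest.** Participant Timeline: "The posttest is completed on tablets (eg, Android tablets) at the intervention location following the final group session". Table 2 puts it at week 8 with a visit window of ±0.
- **Pretest.** Participant Timeline: "The Web-based pretest is completed independently shortly before the first group session". For wait-listed youth this survey is also the control measurement: "the pretest for the wait-list group serves as the follow-up on outcomes for the control group".
- **Setting, second account.** Data Collection describes on-site collection as taking place "via tablets (eg, Android tablets) while at the intervention locations (ie, some Web-based screenings, some pre- and posttests", and the other setting as "independently Web-based (eg, some Web-based screenings, some pretests, or follow-ups".
- **Reminders.** Participant Timeline provides a survey link by email and up to two reminder emails at every time point, 2 and 4 weeks after the initial email.
- **Satisfaction Survey.** Measures calls it "a 20-item questionnaire developed for AFFIRM completed after intervention delivery". No place, device or attendance condition is given, and Table 2 has no row for it.
- **Primary outcome.** Outcomes, Primary: "Acceptability will be assessed through mixed-method participant and facilitator evaluations". The same section counts, under feasibility, how many youth enroll, start and finish.

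**The concern.** A survey collected at the venue when the last session ends reaches those who came to that session. Youth who stopped coming, some of them because they did not like the group, are the ones most likely to be missing. Acceptability is a primary outcome and Hypothesis 1 predicts that it will be high, so under-representing leavers pushes the result towards the hypothesis. The planned imputation is for data judged missing at random. It does not repair non-response that depends on unobserved dissatisfaction.

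The second issue is comparability. Self-reported mood, hope and self-efficacy may shift for a short time after a supportive group meeting. The AFFIRM follow-up is taken at that moment and the wait-list follow-up is not, so part of any difference between conditions may reflect when and where the survey was filled in.

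**Working it through.** The plan states no completion rate, satisfaction rate, effect size or SD, so there is no figure of its own to reproduce. The check sets the passages side by side and adds two illustrations on assumed inputs.

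**1. Reminder timing against the window.** Week 8 is day 8 × 7 = 56. If the posttest link is emailed that day, the reminders fall on day 56 + 14 = 70 (week 10) and day 56 + 28 = 84 (week 12). A ±0 window admits neither. The 6- and 12-month visits have ±14, which admits the first reminder if the email goes out on the target day. The pretest also has ±0, although Participant Timeline describes it as independent and web-based. The ±0 entry therefore shows that schedule and reminders do not fit together. It does not show that remote completion of the posttest is ruled out.

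**2. Who is reached.** Of the surveys in Participant Timeline, the posttest is the only one placed at the venue. Data Collection's examples of independent completion do not name posttests, but that list is only illustrative. No section says that absentees are left out, and none says how they are reached.

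**3. Selection, illustrated.** Let c be the share of starters who respond, s₁ the share satisfied among responders and s₀ the share who would be satisfied among the rest.

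All starters = c·s₁ + (1 − c)·s₀; overstatement = (1 − c)(s₁ − s₀).

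Assume s₁ = 0.90, c from 0.6 to 0.9 and s₀ from 0.4 to 0.8:

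| c | s₀ | All starters | Overstatement |
|---|---|---|---|
| 0.6 | 0.4 | 0.70 | 0.20 |
| 0.7 | 0.6 | 0.81 | 0.09 |
| 0.8 | 0.6 | 0.84 | 0.06 |
| 0.9 | 0.8 | 0.89 | 0.01 |

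The range is 1 to 20 percentage points, and it applies only if non-responders really are not surveyed.

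**4. Place and moment of the two follow-ups.**

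| | AFFIRM posttest | Wait-list pretest |
|---|---|---|
| Place, Participant Timeline | venue | independent, web |
| Place, Data Collection | some at venue | some at venue, some independent |
| Moment | after the last group session | before the first group session |

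The two sections disagree on place. The difference in moment holds under either, because a survey taken before the first session cannot follow a session. All surveys are web-based, so the mode itself does not differ.

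**5. Setting shift, illustrated.** The 2:1 split of about 300 gives 200 and 100. Ignoring clustering, baseline and dropout, the standard error of the difference in SD units is √(1/200 + 1/100) = 0.1225. With no true effect and a pure shift d, the chance of a two-sided 5% result in the direction of the shift is Φ(d/0.1225 − 1.96):

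- d = 0.1: Φ(−1.14) = 0.13
- d = 0.2: Φ(−0.33) = 0.37
- d = 0.3: Φ(0.49) = 0.69

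The values of d are assumptions; nothing in the document supports one over another.

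**The case against.** The other side has several good points. Acceptability draws on facilitators as well as participants. Measures does not tie the Satisfaction Survey to the on-site posttest, and it opens by saying that all measures are completed at all time points, so the survey can be read as also collected at the remote follow-ups. Reminders with a link are promised at every time point, with no exception for the posttest. Data Collection allows some pretests on site, which softens the contrast in place. The outcomes touched by setting are exploratory. Dropout is reported beside satisfaction under feasibility. No acceptability threshold is set, so a lower figure would change no stated decision. Handling of a missed posttest is also the kind of detail that an article may leave to the full protocol.

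Most of this stands, and it rules out two stronger readings. A reader might infer that acceptability comes only from completers. The document does not say so: facilitators contribute, no section limits the survey to completers, and missing session 8 is not the same as failing to complete. A reader might also infer that reminders cannot recover a missed posttest. The reminder text covers every time point, and the pretest carries the same ±0 window while being done remotely.

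Three things survive these points: a stated rule that places the posttest at the venue after the last session, a window that does not match the reminders, and two sections that disagree on setting. These are in the text and are not omissions left to a fuller document.

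**Conclusion.** The point holds in a limited form. Followed as written, posttest collection is likely to under-represent youth absent from session 8. Whether this reaches the participant part of the primary acceptability outcome depends on whether the Satisfaction Survey is given with the posttest, which the document leaves open. The AFFIRM and wait-list follow-ups differ in moment and, under Participant Timeline, in place. This bears on the exploratory comparisons behind Hypotheses 2 and 3 and not on the primary outcomes.

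The size of neither effect can be derived from the document. The 1 to 20 points and the 13%, 37% and 69% rest wholly on assumed inputs and show only that the effects need not be trivial. This is an inexpensive improvement worth making, because the views of leavers who are not asked at the time are hard to recover later. It does not invalidate the plan.

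**What to change.** 1. Reconcile Data Collection with Participant Timeline on where pretests and posttests are completed, and state when and how the Satisfaction Survey is given.
2. Keep tablets for those present at session 8. At week 8, email the existing posttest and Satisfaction Survey link to every participant who started and did not complete on site, whatever their attendance. Those withdrawn from the study under Discontinuation Criteria stay in the count of starters as not surveyed.
3. Widen the posttest window in Table 2 to cover the existing 2- and 4-week reminders.
4. Record setting and date of completion for each survey, and account for them in the AFFIRM versus wait-list comparison. Adjustment can help only in part, because no wait-list follow-up is taken after a group session; name that as a limitation.
5. Report acceptability with the number who started and the number who responded, alongside the result among session-8 attenders.

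The cost is small, since the survey, email list and reminders already exist. The downside is that late posttests will vary in timing by up to about 4 weeks, which is why the completion date should be recorded. Moving attenders off tablets as well would bring the settings closer but could lower response and spread timing further, so it is not needed here.
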